### Eligibility criteria

#### Inclusion criteria

Adult patients (age ≥ 18 years old) with AHRF, diagnosed with non-COVID-19 pneumonia or lung infection, with PaO2/FiO2 ratios of ˃ 100 mmHg and ≤ 300 mmHg, receiving HFNO therapy with a flow velocity ≥ 30 L/min and FiO_2_ ≥ 30% [36], and giving their informed consent will be included in the study.

#### Exclusion criteria

Patients will be excluded from the study if they:Received invasive mechanical ventilation before participating in the experiment during this hospitalisation;Need immediate intubation based on a doctor’s assessment;Are unable to cooperate or refuse to lie in positions of interest;Have haemodynamic instability (Systolic Blood Pressure < 90 mmHg, Mean Blood Pressure < 65 mmHg) or need vasoactive drugs;Have deep venous thrombosis or pulmonary embolism;Have acute haemorrhagic disease;Have thoracic and abdominal trauma or burns, have undergone surgery within three months, or are pregnant;Undrained pneumothorax;Have increased intracranial pressure or spinal cord injury;Terminal-ill patients with a life expectancy of no more than 6 months.

Considering prone position and lateral position may help patients to avoid endotracheal intubation, and patients usually do not decide whether they want to get endotracheal intubation or not until the last moment, so we decided not to exclude patients with “do not intubate” orders.

### Randomisation and concealment

Two investigators who will not participate in this trial will conduct stratified blocked randomisation. First, they will generate random sequences and blocks of various lengths for different centres and layers with IBM SPSS Statistics 25. Then they will obtain grouping results according to the order of the random numbers in different blocks and layers. Subsequently, the grouping results will be placed in opaque sealed envelopes marked with a serial number for the patients’ enrolment order. In addition, they will have a layer mark for the PaO_2_/FiO_2_ ratio category. The envelopes will then be kept by a person who will not participate in the trial at each centre. The person will only open the corresponding envelope when grouping the patients according to their PaO_2_/FiO_2_ ratio (> 200 mmHg or ≤ 200 mmHg) and their enrolment order.

Due to the nature of the interventions, only data collectors and data analysts will be blinded to each participant’s allocation. They will directly extract data from hospitals’ medical and nursing record systems. For unclear information, they will consult trained clinical staff. These staff are asked not to disclose information about patients’ group allocation or the interventions.

### Interventions

We will use Fisher & Paykel Airvo2, Micomme OH-70C, Yuwell HF-75A, Mindray SV300 and other equipment that meets particular requirements for basic safety and essential performance of respiratory high-flow therapy equipment (ISO 80601-2-90:2021). All instruments were provided by the research centres. The researchers in charge of the implementation are nursing team leaders with more than 8 years’ nursing experience. The physicians responsible for disease assessment are doctors with more than 5 years’ experience in ICU diagnosis and treatment.

The parameters of the HFNO therapy system will be set as follows: the initial flow velocity is set at 40–60 L/min. Moreover, FiO2 will be titrated from 30% to maintain pulse oxygen saturation (SpO_2_) at 90%–96%. It will also be dynamically adjusted according to SpO_2_ and blood gas analysis results. If the oxygenation target is not reached, the flow velocity can be gradually increased up to 60 L/min, and FiO_2_ can be increased up to 100%. The temperature ranges from 31℃ to 37 ℃ and will be appropriately adjusted according to each patient’s comfort or tolerance level and sputum viscosity [37].

### Experimental groups

The prone position group (Group A) will take the prone position on a horizontal bed for at least 1 h each time. Patients will be encouraged to take the position as many times as possible each day and remain in the prone position as long as possible each time if they are not tired. The investigators will insert a U-shaped pillow under each patient’s neck or chin and rectangular pillows under their shoulders, chest, hips, knees, and ankles. Then adjust the pillows to ensure their cervical and lumbar vertebrates are in functional positions and patients feel comfortable. Patients’ posture and pillow position can be adjusted at any time with anyone’s help. However, the patients must always keep the abdominal side down and parallel to the bed surface. (More details are provided in Additional file 4).

The lateral group (Group B) will be instructed to alternate lying on each side of their body at an 80°–90° angle on a horizontal bed for at least 1 h each time. Patients with a mono-lateral lung infection will be instructed to lie on the healthy side. Patients will put their upper arms and legs on quilts or pillows placed on the facing side. Their hips will be decompressed to prevent pressure injury. And they will be encouraged to lie on the same side for as long as possible each time and switch to the other side or take the supine position when they feel tired. One round is completed when the patients return to the semi-recumbent position for more than 10 min.

Patients in experimental Groups A and B will be told to change positions at least 1 h after a meal. We track the number of rounds and durations of each round for each assigned position on a daily basis. Only when the patient meets the standards of the corresponding position, and keeps it at least for 1 h at a time, will the duration be considered valid and recorded. Blood gas analysis will be performed daily and 1–2 h after returning to a semi-recumbent position on the first day.

### Control group

Patients in the control group will take the semi-recumbent position (with the bed head elevated 30°–40°) which is the regular position taken by patients. Nurses will routinely instruct the patients to roll over and check vital signs every 2 h. Arterial blood gas will be measured daily. Patients in this group will not take the prone or lateral position unless their doctors think it is necessary.

### Indications for terminating the intervention

When the patient’s flow velocity is < 30 L/min and the PaO_2_/FiO_2_ ratio is > 300 mmHg for 6 h [38];The patient can maintain SpO_2_ at 92%–96% [39] with a respiratory rate no more than 25–30 times per minute while using conventional oxygen therapy (nasal prongs, facemask with or without reservoir or Venturi mask with less than 8 litres per minute and the fraction of inspired oxygen less than 35%).The patient’s condition worsens, noninvasive ventilation or endotracheal intubation is needed (see more in “Indications for noninvasive ventilation” and “Indications for endotracheal intubation” section) or death occurs.

### Strategies to improve adherence to the interventions

We placed eligible patients in the prone position and conducted a qualitative study on factors affecting the implementation of APP in patients and medical staff. And modified the interventions to make them more acceptable.Researchers explain and encourage patients in a standard way (Additional file 2).We will tell patients the potential benefits they may receive and show them the changes in their PaO_2_/FiO_2_ ratio.Patients’ families will be invited to supervise and encourage patients to take the assigned position.Patients will be asked to take the assigned position continuously without interruption.We will address problems affecting patients’ comfort before taking corresponding positions, such as constipation, intestinal flatulence, and pain.We will place commonly used items (such as water bottles, straws, tissues, phones, urinals, and garbage bins) within patients’ reach.We will ask patients to engage in activities that interest them, such as sleeping and watching videos.

### Withdrawal criteria

Patients refuse to undergo HFNO therapy further after enrolment.Patients refuse to change position in the middle of the trial or position change time is <1 h/day.Patients are discharged halfway through the trial.The medical staff thinks that continuing to participate in the study will cause serious harm to the patient.

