### Data collection and management

The outcomes will be measured during the intervention and 28 days after the patients are enrolled in the group. The data on the duration of different respiratory support, hospital and ICU lengths of stay, and hospitalisation cost will be collected at discharge or the 28th day after enrolment, whichever occurs first. (The data collection schedule is shown in Table 1). Trained nurses will assess the Borg scale score and fill in the bedside inspection forms (Additional file 6) with average vital signs within 3 min at each allotted timepoint and position change time of each round. Supervisors will examine and transcribe inspection forms every day. Two trained researchers who do not know patients’ allocations will check and collect all other data extracted from the electronic medical record system, including data on withdrawn patients. The main researchers will explain every detail of the parts each researcher is responsible for through online or physical training with a set of standard teaching materials, check the training effect through a test, and give one-to-one guidance to every researcher according to their results.

**Table 1 Tab1:** Data collection schedule

Study Period	Timepoint	Assessments
Enrolment	Day 0–1	Eligibility
		Informed consent
Allocation		Baseline information
		PaO_2_/FiO_2_ ratio after receiving HFNO therapy for 2 h
Post-allocation	During interventions (Day 1–termination)	Vital signs
		PaO_2_/FiO_2_ ratio
		Borg scale
		Position changing time (experimental groups only)
		ROX index
		Special treatments
		Respiratory support
		Adverse events
	At discharge/Day 28	Hospitalisation cost
		Number of hours using HFNO
		Number of hours using advanced respiratory support mode
		Number of hours using conventional oxygen therapy
		Length of hospital and ICU stay
Close-out	At Day 28	Death
		Endotracheal intubation

The confidentiality of the data will be preserved when the coded, anonymised data are transmitted and stored at the location of the statistician in charge of the final analysis.

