### Methods for additional analyses

We will conduct subgroup analyses based on the PaO_2_/FiO_2_ ratio (PaO_2_/FiO_2_ > 200 mmHg or ≤ 200 mmHg), time from admission to intervention implementation (< 24 h or ≥ 24 h), position changing time, and different diagnoses. The Bonferroni correction will be used for pairwise comparisons among the three groups. We will handle the missing values of withdrawn patients with the intention-to-treat the analysis and use multiple imputation. We will also do a per-protocol analysis if patients in the supine position group take the intervention that the experimental groups have. Since this is a multicentre study, centre-effect analysis will be implemented.

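### Position non-adherence and discharge are withdrawal criteria, and the protocol does not reconcile this with intention-to-treat or with its data collection on withdrawn patients

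*Protocol article*

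**What the plan says.** All references are to the Protocol article.

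- **Withdrawal criteria** has four entries: "Patients refuse to undergo HFNO therapy further after enrolment"; "Patients refuse to change position in the middle of the trial or position change time is <1 h/day"; "Patients are discharged halfway through the trial"; and a staff judgement that continuing would seriously harm the patient. This list is separate from Indications for terminating the intervention, which covers recovery, deterioration and death.
- **Sample size** raises 486 to 583 for 20% dropout, attributed to poor tolerance and pilot experience.
- **Methods for additional analyses**: "We will handle the missing values of withdrawn patients with the intention-to-treat the analysis and use multiple imputation". A per-protocol analysis is mentioned only for controls who take up the experimental positions.
- **Data collection and management**: other data are "extracted from the electronic medical record system, including data on withdrawn patients". Respiratory-support durations "will be collected at discharge or the 28th day after enrolment, whichever occurs first". Table 1 has the entry "Position changing time (experimental groups only" and lists only death and endotracheal intubation at day 28.
- **Control group**: "Patients in this group will not take the prone or lateral position unless their doctors think it is necessary".
- **Objectives and hypothesis** expects that the lateral position may do better than prone because patients tolerate it better.
- **Primary outcomes** counts days free of both invasive and noninvasive ventilation over the 28 days from randomisation.

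**The concern.** Refusing the position, or spending little time in it, happens after randomisation and can be a consequence of the assignment. Controls have no assigned position change and no recorded position time, so the criterion can sensibly operate only in the two experimental arms. If those patients' outcomes go missing and are filled in from patients who kept to the position, the position arms are described by their tolerant members while control is described by everyone. That is closer to an effect-if-tolerated than to the intention-to-treat effect the plan claims. It also works against the trial's own hypothesis, in which tolerance is part of what separates lateral from prone.

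Discharge raises a different problem. Collection of respiratory-support durations stops there, and the day-28 items do not include noninvasive ventilation. For a patient discharged early, the protocol does not say how the remaining days enter the primary outcome: as observed ventilator-free days, or as missing values of a withdrawn patient.

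**Working it through.** **The plan's own figure.** Inputs from Sample size: means 19, 23 and 22 days; SDs 13, 12 and 11; alpha 0.05; power 0.80; one-way ANOVA.

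- Common variance = (169 + 144 + 121)/3 = 144.67, so SD = 12.03.
- Grand mean 21.33; sum of squared deviations = 5.44 + 2.78 + 0.44 = 8.67.
- Noncentrality at 162 per arm = 162 × 8.67/144.67 = 9.7, which gives power 0.800. So 3 × 162 = 486 reproduces, and 486 × 1.2 = 583.2 gives the 583.

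The design therefore plans for intolerant patients to be lost. The allowance would not be needed for them if their outcomes were expected to be observed.

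**Position non-adherence.** Let w be the share of a position arm withdrawn with a missing outcome, and D the shortfall in mean ventilator-free days of those patients against those who stay (mean T).

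- True arm mean = (1 − w)T + w(T − D) = T − wD.
- Arm mean if the missing outcomes are imputed from those who stay = T.
- Upward shift = w × D.

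With no true effect and shift b in both position arms, the noncentrality is 162 × (2/3)b²/144.67 = 0.747b². Assume w = 20% in each position arm and none in control:

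| D (days) | Shift b (days) | ANOVA rejection, 162 per arm |
|---|---|---|
| 0 | 0 | 5% |
| 2 | 0.4 | 5.9% |
| 4 | 0.8 | 8.7% |
| 6 | 1.2 | 13.9% |
| 8 | 1.6 | 21.6% |

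The planned differences from control are 4 days (prone) and 3 days (lateral). Only the overall 20% comes from the documents; the split by arm and every value of D are assumptions. At w = 10% and D = 2 to 8, the shift is 0.2 to 0.8 days and rejection 5.2% to 8.7%. If the whole 20% (0.20 × 583 ≈ 117) fell among the roughly 389 position-arm patients, w would be about 30%, the shift 0.6 to 2.4 days and rejection 7.1% to 44.0%. The calculation ignores the extra variance that multiple imputation adds.

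If the two position arms lose equal shares with equal D, prone against lateral is not shifted. Each 10 percentage points of excess loss in one arm shifts that contrast by 0.1 × D, or 0.2 to 0.8 days for D = 2 to 8, against a planned difference of 23 − 22 = 1 day.

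**Discharge.** Suppose a share q of an arm is discharged early, all truly with 28 ventilator-free days, and is imputed from the rest. The arm mean M becomes (M − 28q)/(1 − q). With M = 19 (control) and 23 (prone), the true difference is 4 days:

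| q control | q prone | Control | Prone | Apparent difference |
|---|---|---|---|---|
| 40% | 40% | 13.0 | 19.7 | 6.7 |
| 40% | 50% | 13.0 | 18.0 | 5.0 |
| 30% | 50% | 15.1 | 18.0 | 2.9 |

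The difference can be inflated or reduced. The shares and the 28 days are assumptions.

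**The sections side by side.** Withdrawal criteria defines the withdrawn group by adherence and discharge. Data collection and management keeps collecting hospital-record data on that group. Methods for additional analyses imputes whatever is missing in it. None of the three says whether withdrawal ends follow-up, or that the collected record supplies the outcome.

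**The case against.** The strongest reply is that the plan does not throw these patients out. It states intention-to-treat, imputes missing values only, and collects record data on withdrawn patients. An intolerant patient who stays in hospital can have a complete ventilation record analysed in the assigned arm. No imputation model is given, so imputing from those who stay is the reviewer's assumption; the model is properly left to an analysis plan. Discharge is itself a planned collection point and length of stay is an outcome, which fits badly with every discharge being a loss. The phrase about discharge halfway through is undefined and could mean leaving during the intervention.

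Much of this stands, and it rules out several stronger readings that a reader might infer:

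- That failures are removed from the position arms, or that every withdrawn patient is imputed. The documents support neither. Nor do they say that intolerant patients have fewer ventilator-free days; if they do not differ, the shift is zero.
- That the less-than-1-hour rule would withdraw all controls. Table 1 confines position time to the experimental groups, so this is plainly not intended.
- That the withdrawal list as a whole acts only in the position arms. Discharge, refusal of HFNO and the harm criterion apply to all.
- That the discharge rule penalises a particular arm, or that every early discharge is a good outcome. The direction is not fixed, and the reasons for discharge are not distinguished.

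The reply does not close the gap. Withdrawal is listed apart from termination of the intervention, the sample size treats intolerance as loss, and no section says that the record data take the place of imputation. Nor is hospital-record collection stated to cover ventilation after discharge.

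**Conclusion.** The point holds as an unresolved conflict within the protocol, not as a demonstrated bias. A stated rule allows post-randomisation loss that, for adherence, is specific to the prone and lateral arms and tied to the very property the trial wants to compare. To the extent that this loss leaves the primary outcome missing, the analysis moves away from the intention-to-treat effect. Under the main illustration (20% of each position arm imputed from those who stay, none in control, no true effect) the position-arm means shift by 0 to 1.6 days for a shortfall of 0 to 8 days, and ANOVA rejection runs from 5% to 21.6%. If observed outcomes are used for everyone, the shift is zero. For discharge, the treatment of later days and of noninvasive ventilation after discharge is open, and the direction of any bias cannot be stated.

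**What to change.** 1. In Withdrawal criteria, reclassify low position time, refusal of the position and discharge as adherence or disposition events that do not end follow-up. This concerns data and analysis only; whether and when positioning stops is a clinical matter outside this point.
2. State that every randomised patient's observed 28-day ventilation and vital status is analysed in the assigned arm, using the record data already collected on withdrawn patients.
3. State that days alive after discharge without ventilation count as ventilator-free. Add noninvasive ventilation to the day-28 items in Table 1, and say how status is obtained for patients who have left hospital.
4. Reserve multiple imputation for withdrawn consent or true loss to follow-up.

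The cost is a wording amendment and one further item at day 28. The protocol describes no patient contact at day 28, so obtaining ventilation status after discharge may need a small additional step. The effect estimate will be diluted by non-adherence, but that is the intention-to-treat effect the plan says it wants.

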### Indications for endotracheal intubation

Severe respiratory failure does not improve or worsens after noninvasive or high-flow treatment.The patient’s respiratory pattern is seriously abnormal; the frequency is > 40 breaths per minute or < 6–8 breaths per minute; the patient has irregular breathing, weak spontaneous breathing, or disappearance of breath.The patient’s consciousness level decreases, and the Glasgow Coma Scale score is < 10 points.The partial pressure of carbon dioxide increases progressively, and the pH value is <7.25.Airway obstruction that cannot be relieved in the short time.

### Indications for noninvasive ventilation

No obvious improvement or aggravation was found in the use of nasal high-flow oxygen therapy (respiratory > 35 times per minute, SpO2 < 88%, paradoxical thoracoabdominal motion, continuous use of adjunctive respiratory muscle)Arterial blood gas analysis showed that PH < 7.35, partial pressure of carbon dioxide > 45 mmHgThe ROX index [40] (SpO_2_/FiO_2_ to respiratory rate) < 2.85, < 3.47, < 3.85 after the use of HFNO therapy for 2 h, 6 h, or 12 h respectively, or the above situation occurred within 48 h.The patient cannot maintain SpO_2_ > 90% with FiO_2_ ≥ 60% and a flow velocity of 60 litres per minute via HFNO.

Weaning indications from mechanical ventilation are seen in Additional file 5.

These criteria were all learned and agreed upon by doctors in different centres. The doctors will mainly evaluate whether patients need mechanical ventilation according to the standards above. Investigators will record and evaluate any other reasons for performing mechanical ventilation, as well as cases that meet the criteria but do not get mechanical ventilation.

### Provisions for post-trial care

Routine diagnosis, treatment, and nursing will be determined according to each patient’s condition.

### Outcomes

#### Primary outcomes

The primary outcome variable is ventilator-free days in 28 days. It is defined as days free from invasive mechanical ventilation or noninvasive ventilation within 28 days after randomisation.

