## Methods

### Trial design

This is a three-arm, parallel-group, multicentre, randomised controlled, open-label exploratory trial. A total of 583 will be randomly assigned to be placed in the semi-recumbent position (control group), the prone position (experimental Group A), and the lateral position (experimental Group B) at a ratio of 1:1:1. The follow-up period was 28 days. We will conduct and report this trial according to Standard Protocol Items: Recommendation for Interventional Trials. The trial design flowchart is detailed in Fig. 1.

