### Sample size

We calculated the sample size with NCSS statistical software PASS 2021 (version number: 21.0.3). The estimation of ventilator-free days in 28 days for the control group was 19 days, with a standard deviation of 13, based on what was reported before [29] and the severity of the disease [30, 31]. After being placed in the prone position and lateral position, the ventilator-free days in 28 days are expected to increase to 23 days and 22 days, and a standard deviation of 12 and 11 respectively, according to the mean difference in recent researches [10, 29] and the potential benefits of the refined interventions [16, 32–35]. Using an analysis of variance model with a two-sided alpha level of 0.05 and a power of 0.8. The allocation ratio is 1:1:1, so 486 participants are needed. We estimated a dropout rate of 20% due to poor tolerance and our experience in the pilot trial, so a total of 583 patients will be enrolled.

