### Statistical methods for the primary and secondary outcomes

Analysis of variance will be used for ventilator-free days in 28 days, the number of hours using HFNO, noninvasive ventilation, invasive mechanical ventilation, length of hospitalisation, and hospitalisation cost. When it indicates that at least one group is significant, the Bonferroni correction will be applied.

For the 28-day mortality rate and 28-day intubation rate, we will conduct a survival analysis with the Kaplan-Meier method. We will compare the mortality and intubation rates of the three study groups using a log-rank test. We will use the Cox proportional hazards model to detect the relationship between diagnosis, onset time, PaO_2_/FiO_2_ ratio change, the duration of changing positions, and total position changing time.

Other secondary outcomes, such as the change in the PaO_2_/FiO_2_ ratio, ROX index, Borg scale score within the groups, will be compared with a paired repeated measures analysis of variance or generalised estimating equation based on the integrity of the data. The incidence of adverse events will be analysed using either the chi-square test or Fisher’s exact test. Univariate and multivariate analyses of risk factors for prone position failure will be performed with logistic regression.

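### The primary outcome has no rule for death, so patients who die can score as well as or better than surviving patients who were ventilated

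*Protocol article*

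**What the plan says.** Primary outcomes: "It is defined as days free from invasive mechanical ventilation or noninvasive ventilation within 28 days after randomisation". Under Trial design, "The follow-up period was 28 days". Neither statement mentions survival.

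The analysis is given under Statistical methods for the primary and secondary outcomes: "Analysis of variance will be used for ventilator-free days in 28 days". No treatment of deaths is attached to it.

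Other sections where a rule might be expected do not contain one:

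- Withdrawal criteria do not list death.
- Methods for additional analyses covers missing values of withdrawn patients, by intention to treat and multiple imputation. It does not cover death.
- Secondary outcomes lists 28-day mortality separately and includes death in treatment failure. Neither feeds into the primary outcome.

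Background and rationale cites, for HFNO, a failure rate of 48%, intubation in 43% and 28-day mortality of 19%. On do-not-intubate orders, Exclusion criteria says "so we decided not to exclude patients with" them. Sample size gives the control value: "The estimation of ventilator-free days in 28 days for the control group was 19 days, with a standard deviation of 13". The prone and lateral means are "expected to increase to 23 days and 22 days, and a standard deviation of 12 and 11 respectively".

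**The concern.** Death stops ventilation. If the score counts days off the ventilator and ignores survival, then for two patients with the same course up to a given day, the one who dies that day can never score lower than the one who lives, because only the survivor can still accrue ventilator days. The score therefore treats death as neutral at worst and as a benefit at best.

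At the mortality the article expects, this affects roughly one patient in five. The primary comparison could show no difference when one position carries more deaths, or could favour that position. The wording also allows at least three derivations (all days count, only days alive count, death scores 0), and these give different answers from the same data.

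**Working it through.** **The plan's own figure.** Inputs from Sample size: means 19, 23, 22; SDs 13, 12, 11; two-sided alpha 0.05; power 0.8; allocation 1:1:1. The pooled SD is √((13² + 12² + 11²)/3) = 12.03. One-way analysis of variance with the noncentral F distribution gives 162 per arm, 486 in total, with power 0.800. The stated 486 is reproduced. The planned prone effect is 23 − 19 = 4 days.

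**Individual scores.**

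| Patient | All days count | Only days alive count | Death = 0 |
|---|---|---|---|
| Dies day 3, never ventilated | 28 | about 3 | 0 |
| Dies day 6 after 3 ventilated days | 25 | about 3 | 0 |
| Dies day 20, never ventilated | 28 | 20 | 0 |
| Survives, ventilated 10 days | 18 | 18 | 18 |

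Under the first reading all three deaths outscore the survivor. Under the second, the day-20 death still does.

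**Size, first illustration.** Assumptions: 48% ventilated (the cited failure rate, used as the ventilated share), 8.5 ventilator days each, and death in 30% of ventilated and 8% of unventilated patients. Durations and split are not in the documents. Mortality is 0.48 × 0.30 + 0.52 × 0.08 = 0.186, about 19%.

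- As written: 28 − 0.48 × 8.5 = 23.9.
- Death = 0: 0.52 × 0.92 × 28 + 0.48 × 0.70 × 19.5 = 13.40 + 6.55 = 19.9.
- Gap: 4.0 days.

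Now let 10% of all randomised patients die who would have survived after ventilation, with ventilator time unchanged. As written the mean stays at 23.9. With death = 0 it becomes 19.95 − 0.10 × 19.5 = 18.0. Mortality among the ventilated rises from 30% to (0.144 + 0.10)/0.48 = 51%. A rise from 30% to 40% among the ventilated would give 13.40 + 0.48 × 0.60 × 19.5 = 19.0 instead. This illustration shows blindness to deaths, not reversal.

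If instead 5% of patients die rather than being ventilated, the as-written mean rises by 0.05 × 8.5 = 0.4 and the death = 0 mean falls by 0.05 × 0.70 × 19.5 = 0.7. That is a reversal, though a small one.

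**Size, second illustration.** Assumptions: ventilated survivors 10 days, ventilated deaths 5 days, death on day 10. Reference arm: 5% die unventilated, 14% die ventilated, 29% survive ventilated, 52% survive unventilated. Worse arm: 10 points of the ventilated survivors die instead (29% dead in total), after 5 ventilated days or without ventilation.

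| Rule | Reference | Worse, ventilated deaths | Worse, unventilated deaths |
|---|---|---|---|
| All days count | 24.40 | 24.90 | 25.40 |
| Only days alive count | 20.98 | 19.68 | 20.18 |
| Death = 0 | 19.78 | 17.98 | 17.98 |

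Read literally, the arm with more deaths looks better by 0.5 to 1.0 day. With death = 0 it is worse by 1.8 days. For extra deaths among the ventilated, with survivors ventilated 6 to 14 days and deaths 2 to 8 days, the literal difference runs from −0.2 to +1.2 days and the death = 0 difference from −1.4 to −2.2.

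**The case against.** The strongest reply is that the text is silent rather than wrong. It does not say that days after death count, and the article condenses a fuller protocol, now in its fourth version, that may hold the rule. The silence is real, and the literal score of 28 for an early death is one reading only. But the article does define its primary variable, the definition omits the event that most affects it, and the days-alive reading still lets some deaths outscore survivors.

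Excess deaths would also be seen elsewhere: in the mortality analysis, in treatment failure and by the data monitoring committee. The trial calls itself exploratory. All of that stands and limits the harm, but it does not make the primary result interpretable.

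Keeping do-not-intubate patients makes deaths without invasive ventilation possible. This adds less than it seems to, because noninvasive ventilation also counts against the score. A full 28 at death needs neither kind.

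Three stronger readings are tempting and are not supported:

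- *That every death outscores every survivor.* A death after 10 ventilated days scores 18 on the literal reading, against 28 for a never-ventilated survivor.
- *That the planning values prove a death = 0 convention.* For the control arm, 28 × 19 − (13² + 19²) = 2, so nearly all patients would sit at 0 or 28, with about 9/28 = 32% at 0. That is suggestive. But the prone mean of 23 with SD 12 exceeds the largest SD possible on a 0–28 scale, √(23 × 5) = 10.72, under any rule for death. SDs this unreliable cannot reveal which convention was used. Nor does the first illustration with death = 0 reproduce SD 13: √(0.4784 × 28² + 0.336 × 19.5² − 19.95²) is about 10.2.
- *That the analyses of support hours, length of stay and cost fail for the same reason.* How deaths are handled there is detail commonly left to an analysis plan.

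**Conclusion.** The concern holds as a missing rule in the definition of the primary outcome. Deaths can score as well as or better than ventilated survivors, and the primary analysis can miss excess mortality or favour the arm that has it. Reversal between arms is possible, not certain.

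The two firm elements are the absence of any rule and the ordering of individual scores, which need no assumption beyond the reading adopted. The group-level sizes (a 4-day gap between scoring rules, and a shift of roughly −0.2 to +1.2 days in the literal score when 10 points of ventilated survivors die after ventilation) rest on assumed ventilator times and an assumed split of deaths. The documents give neither, so these figures show scale and are not forecasts. Whether the sample-size inputs used a different definition from the stated one cannot be settled from the documents.

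**What to change.** Under Primary outcomes, define ventilator-free days as days alive and free of invasive and noninvasive ventilation from randomisation to day 28, with 0 for any patient who dies by day 28. If the full protocol already holds a rule for death, state it in the definition. Other explicit conventions exist, such as a ranking with death worst, but scoring death as 0 keeps the planned analysis in place.

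Under Sample size, confirm that the means and SDs refer to that same definition, and correct them if they do not. No revised sample size can be derived here, because the documents give no distribution of the outcome by survival status.

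The cost is one sentence and a changed derivation. Death at day 28 is already collected (Table 1), so no extra patients or visits are needed. The change should be made and dated before any comparison of outcomes by arm.
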